## Abstract

**Introduction:**

Bacterial translocation and gut dysbiosis are key drivers of systemic immune activation in decompensated cirrhosis, precipitating inflammatory complications such as acute-on-chronic liver failure (ACLF). Currently, no licensed therapies effectively restore intestinal barrier function or reverse dysbiosis in this vulnerable population. While previous studies have suggested benefits of faecal microbiota transfer (FMT) in hepatic encephalopathy or alcohol-associated hepatitis, data on its safety and immunomodulatory effects in decompensated cirrhosis with ascites are lacking. This Phase IIa trial (TransImmune) aims to evaluate the safety and tolerability of encapsulated FMT. Furthermore, it will assess feasibility, microbial engraftment and downstream effects on intestinal barrier integrity, as well as systemic and peritoneal inflammation.

**Methods and analysis:**

This is a prospective, single-centre, randomised, double-blind, placebo-controlled Phase IIa pilot study. A total of 24 patients with decompensated cirrhosis and ascites will be randomised in a 1:1 ratio to receive either encapsulated FMT or placebo over three consecutive days. The investigational product, INTESTIFIX 001, is an encapsulated FMT preparation derived from rigorously screened healthy donors and manufactured under Good Manufacturing Practice (GMP) conditions with predefined release specifications, including minimum alpha-diversity QC criteria, manufactured by the Cologne Microbiota Bank (CMB). The primary endpoints are the occurrence of serious adverse events (SAE) up to the end of study (EOS) and the occurrence and severity of treatment-emergent adverse events (TEAE). Secondary endpoints evaluate signals of clinical efficacy, specifically: (1) systemic inflammation (white blood cell count, C-reactive protein, procalcitonin and IL-6); (2) gut inflammation (faecal calprotectin); (3) organ dysfunction (Child-Pugh, MELD and CLIF-SOFA scores); (4) quality of life (EQ-5D-5L and CLDQ) and (5) the number of antibiotic-free days. Patients will be monitored across five study visits up to 90 days.

**Ethics and dissemination:**

The study was approved by ethics committee review and the German Federal Institute for Drugs and Medical Devices (BfArM). The trial is registered under EU CT no. 2023–5 07 790-18-00. The results of the study will be disseminated via peer-reviewed publications and at international conferences.

**Trial registration number:**

EU Clinical Trials Register: 2023-507790-18-00. Registered on 8 August 2024.

STRENGTHS AND LIMITATIONS OF THIS STUDYThe trial uses a randomised, double-blind, placebo-controlled design, with placebo capsules that are indistinguishable from the active preparation in appearance, weight and taste.A GMP-grade faecal microbiota transfer (FMT) preparation (INTESTIFIX 001), manufactured to standardised procedures and predefined release specifications, minimises manufacturing-related and handling-related batch-to-batch variability and allows non-invasive oral administration without endoscopy, while the inherent donor-to-donor batch variability of allogeneic FMT is documented and explored descriptively.A multi-compartment sampling approach (blood, stool and ascites) is applied to assess microbial engraftment, intestinal barrier function, and both systemic and peritoneal inflammation.As a single-centre pilot study with a small sample size (n=24), the trial is designed to assess safety and feasibility, and its statistical power for clinical efficacy endpoints is very limited.Concomitant medications that are often unavoidable in this population (eg, lactulose, proton pump inhibitors and antibiotic prophylaxis) may confound interpretation of microbiome changes, an effect that randomisation distributes across arms but does not eliminate.

## Introduction

 Chronic liver disease represents a major global health burden. In Europe alone, more than 29 million people suffer from chronic liver disease, resulting in approximately 170 000 deaths annually.^1^ While the early stages of the disease are often asymptomatic, the progression to liver cirrhosis marks a critical turning point. Recent data indicate that patients with cirrhosis have the highest in-hospital mortality rate compared with other chronic diseases, with mortality exceeding 17% in those with complicating bacterial infections.^2^ To improve outcomes in this vulnerable population, it is essential to understand the underlying mechanisms that drive the transition from stable, compensated cirrhosis to the acute decompensation phase characterised by organ failure and high mortality.

While the underlying aetiology drives the development of cirrhosis, a key mechanism underlying its progression to decompensation is the dysfunction of the gut-liver axis. Physiologically, the liver acts as a gatekeeper, filtering blood from the intestine and preventing harmful substances from entering the systemic circulation.^3^ In advanced cirrhosis, however, this protective relationship breaks down. The physiological barriers, mucoepithelial, endothelial, and immunological, fail, facilitating the translocation of viable bacteria and microbial products from the intestinal lumen into the portal and systemic circulation.^4^ This process is not merely a consequence of portal hypertension but a key driver that perpetuates systemic inflammation, exacerbates portal hypertension and accelerates the development of acute-on-chronic liver failure (ACLF).^5
6^

Barrier failures in cirrhosis are linked to alterations in the intestinal ecosystem known as gut dysbiosis.^3
7^ Patients with cirrhosis exhibit quantitative and qualitative changes in their microbiota, including small bowel intestinal overgrowth and distinct patterns such as the enrichment of oral commensals (eg, *Streptococcus* and *Veillonella* species) alongside an increase in potentially pathogenic *Enterobacterales*.^8^ This altered microbiota is mechanistically implicated in the progression of metabolic dysfunction-associated steatotic liver disease (MASLD) and alcohol-related liver disease (ALD). Elevated luminal concentrations of ethanol, acetaldehyde and acetate, combined with depleted levels of barrier-protective butyrate and long-chain fatty acids correlate with disrupted tight junction proteins and decreased luminal antimicrobial peptides.^9^

In a healthy state, bacteria that breach the gut barrier and enter portal circulation are efficiently captured and cleared by hepatic Kupffer cells. However, in cirrhosis, this clearance capacity is significantly impaired.^10
11^ Consequently, bacterial products can enter the systemic circulation and then inflammation intensifies and circulating immune cells, such as monocytes, develop a dysfunctional state of altered innate immune memory and immune deficiency.^12–14^ These inflammatory events perpetuate a vicious cycle of translocation and systemic immune activation, significantly increasing the risk of bacterial infections.

Currently, therapeutic options to break this cycle are limited. No licensed therapies effectively reverse dysbiosis or strengthen intestinal barrier function in patients with decompensated cirrhosis and ascites. The management of ACLF remains largely supportive, targeting organ failure rather than the underlying microbial drivers.^15^ Faecal microbiota transfer (FMT) has emerged as a promising strategy to restore microbial diversity and homeostasis. While FMT is established for *Clostridioides difficile* infection,^16^ its application in liver disease is under active clinical evaluation, with several randomised trials now reporting preliminary efficacy data.

Small, controlled trials have demonstrated potential benefits of FMT in MASLD (improving insulin sensitivity and permeability),^17–19^ hepatic encephalopathy (HE; improving cognition, dysbiosis and quality of life)^20–22^ and alcohol-associated hepatitis (improving ACLF and potential survival).^23–26^ Concurrently, large ongoing trials like the UK PROMISE trial (ISRCTN17863382) and the Danish ChiFT trial (NCT04932577)^27^ are evaluating clinical endpoints in broader populations with cirrhosis.

### Rationale for the TransImmune trial

Despite these advances, a critical evidence gap remains regarding patients with cirrhosis and ascites. The presence of ascites is a major predictor of intestinal permeability and poor infection-free survival.^28^ Patients with ascites exhibit the most severe gut barrier dysfunction and the highest infection risk, yet remain systematically under-represented in FMT trials, which have largely enrolled stable outpatient cohorts—a gap the TransImmune trial is specifically designed to address.

Establishing the safety profile in this specific cohort is paramount. Currently, the majority of FMT safety data is derived from patients without liver disease (eg, CDI), where adverse events (AEs) occur in approximately 19% of procedures (mostly mild diarrhoea or abdominal pain), with serious adverse events (SAEs) remaining rare at 1.4%.^29^ Regarding immunocompromised patients, current literature generally supports FMT application due to an acceptable risk profile,^30^ yet severe outcomes, including treatment-related infections, colectomies and death, have been observed in isolated cases among severely immunosuppressed patients.^31^

In patients with cirrhosis, the safety landscape is more nuanced. In a multicentre cohort of patients with cirrhosis undergoing FMT for CDI, FMT-related AEs occurred in 30.2% (mostly self-limited abdominal cramping or diarrhoea) and FMT-related SAEs in 7.9%.^32^ A systematic review of case series has identified severe infectious complications, including *Escherichia coli* bacteraemia and spontaneous bacterial peritonitis, occurring shortly after FMT.^33^ In contrast, prospective randomised trials in cirrhotic cohorts have demonstrated a favourable safety profile. Prospective trials using both enema and capsule formulations reported no increase in SAEs compared with standard care and even a reduction in hospitalisations and alcohol craving in specific subgroups.^21
22
34^ Most recently, the Phase II THEMATIC trial confirmed this trend, reporting no FMT-related SAEs among 60 patients with cirrhosis and HE.^20^ These trials, however, largely excluded patients with advanced organ dysfunction and ACLF, and safety data cannot be directly extrapolated to patients with ascites and profound immune dysfunction, who are at the highest risk for bacterial translocation and infection.

Furthermore, the potential transmission of multidrug-resistant organisms (MDRO) represents a critical safety concern that necessitates rigorous donor screening protocols.^35
36^ Although restoration of a healthy microbiome has been shown to reduce antibiotic resistance genes in the gut,^37^ the potential risk of introducing pathogens remains.

To address these challenges, we use INTESTIFIX 001, a standardised, encapsulated FMT preparation derived from healthy donors with high alpha-diversity, manufactured by the Cologne Microbiota Bank (CMB). This Phase IIa pilot study aims to evaluate the safety and tolerability of this standardised intervention in patients with decompensated cirrhosis and ascites. Furthermore, it will assess feasibility, microbial engraftment and signals of efficacy regarding intestinal barrier integrity, as well as systemic and peritoneal inflammation.

## Methods and analysis

### Study design

TransImmune is an investigator-initiated, prospective, single-centre, randomised, placebo-controlled, double-blind phase IIa trial conducted at the University Hospital RWTH Aachen, Germany, to investigate the safety and tolerability of the FMT product INTESTIFIX 001 in subjects aged 18 to 70 years with decompensated liver cirrhosis and ascites. The study will recruit 24 patients with confirmed cirrhosis and ascites requiring paracentesis or diagnostic tap. The trial is designed in a parallel-group design with two arms randomised in a 1:1 ratio (12 patients INTESTIFIX 001, 12 patients placebo).

### Objectives

The *primary objective* is to evaluate the safety of faecal microbiota transfer (FMT) capsules for the treatment of immune activation in patients with cirrhosis and ascites. The primary endpoints are:

The occurrence of serious adverse events (SAEs) recorded at any time during the study, from inclusion until the end of study (EOS) visit.The occurrence and severity of treatment-emergent adverse events (TEAE) and adverse events (AE).

The *secondary objective* is to evaluate signals of clinical efficacy regarding immune activation. Endpoints to assess the secondary objective are as follows:

Systemic inflammation: Differences in white blood cell count, C-reactive protein, procalcitonin and IL-6 between baseline (day 0) and V3 (day 7±2), V4 (day 28±3), and EOS (day 90+14).Gut inflammation: Differences in faecal calprotectin between baseline (day 0) and V3 (day 7±2), V4 (day 28±3), and EOS (day 90+14).Organ dysfunction: Differences in Child-Pugh score, model of end-stage liver disease (MELD) score, chronic liver failure-sequential organ failure assessment (CLIF-SOFA / CLIF-C OF) score between baseline (day 0) and V3 (day 7±2), V4 (day 28±3), and EOS (day 90+14).Quality of life: Differences in EQ-5D-5L and CLDQ score between baseline (day 0) and EOS (day 90+14).Antibiotic-free days: Number of days without antibiotic use (except for oral use of norfloxacin or rifaximin) between baseline (day 0) and EOS (day 90+14).

The *exploratory objectives* of this trial aim to evaluate the effectiveness of strain engraftment from the FMT products by shotgun metagenomic sequencing, the longevity of the graft and how these factors affect the intestinal barrier function, as well as systemic and peritoneal inflammation. Exploratory analyses include but are not limited to serum and ascitic fluid markers of immune cell activation, systemic inflammation, acute-phase response and immune activation; the composition of the faecal microbiome, virome and mycobiome by shotgun metagenomic sequencing; circulating and faecal markers of intestinal permeability, colonic inflammation and bacterial translocation; and the frequency, differentiation, cytokine repertoire and cytotoxicity of immune cell subsets in blood and, where clinically indicated, in ascitic fluid—each assessed longitudinally from baseline (day 0) through day 7 (±2), day 28 (±3), and end of study (day 90±14).

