### Sample size

As an exploratory Phase IIa pilot trial, the primary purpose is to estimate effect sizes and event rates rather than to perform confirmatory hypothesis testing. Therefore, the width of the 95% CI for the difference in event rates was used as the criterion for sample size calculation. A sample size of 10 evaluable subjects per arm will result in a CI width for the difference of two rates between 0.74 and 0.82 (assuming equal proportions) and ranging between 0.2 and 0.5 using the score method of Miettinen and Nurminen.^38^ Furthermore, 10 subjects per arm ensure that adverse events occurring with a frequency of more than 15% will be detected with a probability of 80%. To account for a potential drop-out rate of approximately 17% (including premature withdrawal and serious protocol violations), a total of 24 participants (12 per arm) will be randomised. Drop-outs will not be replaced.

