### Follow-up

Following the screening phase (V0) and the baseline/randomisation visit (V1), the treatment phase spans 3 days (Visits 2, 2b and 2 c), during which the IMP is administered and acute tolerability is monitored. The subsequent follow-up phase includes an end-of-treatment visit at day 7 (±2 days, V3), a follow-up visit at day 28 (±3 days, V4) and the end-of-study visit at day 90 (+14 days, V5) (figure 1).

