### Statistical analysis

The intention-to-treat (ITT) population includes all randomised patients and will be used for efficacy signals, while the safety (SAF) population includes all randomised patients who took at least one capsule of the IMP and will be used for the primary safety analysis. For the primary endpoint, the percentage of participants experiencing at least one treatment-emergent serious adverse event (SAE) in the INTESTIFIX 001 group will be compared with the placebo group within the safety population up to the end of the study. Given the exploratory nature of this Phase IIa pilot trial, descriptive statistical methods will be employed, and all inferential statistics will be interpreted as hypothesis-generating rather than confirmatory. This approach facilitates the preliminary assessment of efficacy signals and provides data to inform the design of future confirmatory trials.

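### Antibiotic-free days are counted to an end-of-study visit that may fall on any day from 90 to 104, so visit scheduling enters the score day for day.

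*Protocol article*

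**What the plan says.** In the protocol article, Objectives lists five groups of secondary endpoints. The last is antibiotic-free days: "Number of days without antibiotic use (except for oral use of norfloxacin or rifaximin) between baseline (day 0) and EOS (day 90+14"). It is a number of days. No rate, proportion of observed days or fixed cut-off is given.

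Follow-up sets the closing visit as "the end-of-study visit at day 90 (+14 days, V5"), a one-sided window from day 90 to day 104. Safety uses the same one-sided window. The exploratory paragraph of Objectives writes "end of study (day 90±14") instead.

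Statistical analysis states: "The intention-to-treat (ITT) population includes all randomised patients and will be used for efficacy signals". It also makes the analysis descriptive and hypothesis-generating. Study design gives "two arms randomised in a 1:1 ratio (12 patients INTESTIFIX 001, 12 patients placebo").

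**The concern.** For a laboratory value or a score, a visit window is ordinary tolerance, because the measurement is taken a few days later and means much the same. A day count behaves differently. Each day that the visit is delayed adds one day to the score of any patient who is off antibiotics that day, so the window becomes part of the outcome.

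Two patients with identical antibiotic use can therefore score differently, and two with different use can be ranked the wrong way round. At stake is whether the arm means of this endpoint can be read as antibiotic use. The trial is meant to inform the design of later confirmatory trials, so the number should be interpretable even though it is only described.

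**Working it through.** **Plan's own figures.** The article states no figure for antibiotic-free days. The figures under Sample size concern event rates and can be reproduced for 10 per arm:
- The Miettinen-Nurminen 95% widths are 0.742, 0.786, 0.812 and 0.820 at equal rates of 0.2, 0.3, 0.4 and 0.5, against the stated 0.74 to 0.82.
- The chance of seeing at least one event of 15% frequency is 1 − 0.85^10 = 0.803, against the stated 80%.
- For drop-out, 20/(1 − 1/6) = 24.

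None of these depends on the endpoint discussed here.

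**Inputs.** The count starts at day 0 and ends at the end-of-study visit (Objectives). That visit falls on day 90 to 104 (Follow-up). There are 12 patients per arm (Study design). Course lengths of 5, 7, 10 and 14 days are illustrative assumptions.

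**Step 1: score as defined.** Score = visit day − antibiotic days. Whether day 0 itself counts shifts every score equally and changes nothing below.
- No antibiotics: 90 if seen on day 90, 104 if seen on day 104. The range is 14 days, and 14/90 = 15.6%.
- 7-day course, seen on day 104: 104 − 7 = 97, above 90.
- 10-day course, seen on day 104: 104 − 10 = 94, above 90.
- 14-day course, seen on day 104: 104 − 14 = 90, a tie.

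So a course under 14 days can be outweighed, and one of 14 days can only be tied.

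**Step 2: how often.** Assume that both patients' visit days are independent and uniform over the 15 days from 90 to 104, giving 225 equally likely pairs. The treated patient scores strictly higher when the visit gap exceeds the course length:
- 5 days: 45/225 = 20%
- 7 days: 28/225 = 12%
- 10 days: 10/225 = 4%
- 14 days: 0/225 = 0%

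**Step 3: noise in the arm comparison.** Under the same assumption:
- SD = √((15² − 1)/12) = √18.67 = 4.32 days.
- 95% half-width of the arm-mean difference from timing alone = 1.96 × 4.32 × √(2/12) = 3.5 days.
- One 7-day course moves an arm mean by 7/12 = 0.58 days, so 3.5/0.58 is about six such courses in one arm.

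The documents do not give the actual spread of visit days. If all visits fell on one day, the half-width would be 0. At the other extreme, with half on day 90 and half on day 104, the SD is 7 and the half-width is 1.96 × 7 × √(2/12) = 5.6 days.

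**Step 4: the same patients over a fixed day 0 to 90.** No antibiotics scores 90, a 7-day course 83, a 10-day course 80 and a 14-day course 76, whatever the visit date. Timing contributes 0 days, and among patients followed to day 90 the order follows antibiotic use.

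**The case against.** The strongest reply is that this changes little. The endpoint is secondary, the analysis is descriptive, the article concedes very limited power for efficacy, and the sample size does not rest on it. The 94-against-90 case needs one patient on the last permitted day and the other on the first. With uniform visits, a 10-day course wins in only about 4% of pairs. Randomisation and double blinding give no reason for visit dates to differ by arm, so the artefact is noise. All of that stands, and it limits the importance. It does not remove the defect: the definition is stated in the article, and an analysis plan that stopped the count at day 90 would be changing it.

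Some stronger readings are tempting, but the documents do not support them:
- **That the endpoint rewards death, or cuts a withdrawn patient off at withdrawal.** The article does not say how either is scored. A condensed article commonly leaves this to the full protocol or the analysis plan, so the silence is no error.
- **That the count can end as early as day 76.** The two-sided window is attached to the exploratory assessments only. This endpoint carries its own one-sided window, which Follow-up and Safety confirm.
- **That this is the trial's only view of infection.** The article does not call it an infection measure. New infections are assessed at each visit, and adverse events are recorded to the end of study.

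**Conclusion.** The point holds for the floating end of the count. The stated definition and window alone put up to 14 days (15.6%) of scheduling into the score and allow any course shorter than 14 days to be outweighed.

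The size of the noise rests on an assumption about visit dates. With uniform dates, the half-width from timing is about 3.5 days at 12 per arm, within a possible range of 0 to 5.6 days. How this compares with the natural spread of antibiotic use cannot be said, because the article gives no figure for that. A reader might infer that the comparison between arms is biased. Nothing in the documents supports this, since bias would need visit timing to differ by arm. The importance is minor to moderate.

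**What to change.** Define the endpoint over a fixed interval, day 0 to day 90, for every patient regardless of the date of the end-of-study visit. One suitable form is days alive and free of antibiotics, keeping the existing exception for norfloxacin and rifaximin, so that days after death cannot count as antibiotic-free.

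No new data are needed. Concomitant medications are recorded continuously (Follow-up), and the one-sided window means that every completer reaches day 90. The change can be made while the trial is blinded, before the database lock planned for the second quarter of 2027.

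There are two costs. Days 91 to 104 no longer contribute to this endpoint, although they remain in safety follow-up. The days-alive form also lets mortality move the result: a death on day 30 without antibiotics scores 30 and lowers the mean of a 12-patient arm by (90 − 30)/12 = 5.0 days, so deaths should be shown beside it. A separate rate or proportion for patients who withdraw would not combine with a 0-to-90 count, so it is not proposed here.

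Separately, reconcile the end-of-study window within Objectives, where the exploratory text has ±14 days and the secondary endpoints, Follow-up and Safety have +14. This is a wording correction and does not alter the range of the present endpoint.

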### Safety

Safety monitoring is the primary objective of this trial. Adverse events (AEs) are recorded from the time of informed consent until the end of the study at day 90 (+14 days, V5). The severity of AEs is graded according to the National Cancer Institute Common Terminology Criteria for Adverse Events (NCI-CTCAE) V. 5.0. Any serious adverse event (SAE) must be reported to the sponsor within 24 hours of awareness. The sponsor is responsible for reporting Suspected Unexpected Serious Adverse Reactions (SUSARs) to the EudraVigilance database and relevant ethics committees in accordance with the Clinical Trials Regulation (EU) No 536/2014. An independent data and safety monitoring board (DSMB), comprising two clinicians and an independent biostatistician, continuously monitors participant safety throughout the trial; the schedule and criteria for its safety reviews are pre-specified in the DSMB Charter in addition to ad hoc reviews triggered by any safety concern.

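### The end-of-study visit has two different windows, and the primary SAE percentage runs to that visit with early leavers counted as event-free

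*Protocol article*

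**What the plan says.** All references are to the protocol article.

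- **Window of V5/EOS.** Under Objectives, the secondary endpoints use "between baseline (day 0) and EOS (day 90+14" and the exploratory objectives use "and end of study (day 90±14". Follow-up defines "the end-of-study visit at day 90 (+14 days, V5". Safety records adverse events "until the end of the study at day 90 (+14 days, V5".
- **Primary period.** Under Objectives, SAEs count "from inclusion until the end of study (EOS) visit".
- **Primary measure.** Statistical analysis compares "the percentage of participants experiencing at least one treatment-emergent serious adverse event (SAE" between the arms "within the safety population up to the end of the study". The safety population is every randomised patient who took at least one capsule.
- **Losses.** Sample size allows for a "drop-out rate of approximately 17% (including premature withdrawal and serious protocol violations", without replacement. Under Discontinuation and early termination, patients who stop the product but keep their consent stay in safety follow-up.
- **Purpose.** Sample size says the trial is meant to estimate effect sizes and event rates, not to test hypotheses.

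**The concern.** One visit cannot have both windows. Under ±14 a V5 at day 76 is in window; under +14 it is a deviation. The exploratory samples have no visit of their own: Follow-up describes one day-90 time point and one V5. The date of that visit also ends the patient's SAE count, so the discrepancy reaches the primary endpoint.

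The second part concerns the measure. A percentage with everyone dosed in the denominator assumes that each patient was observed to the end. A patient who withdraws consent at day 10 without an SAE stays in the denominator, and any later SAE goes unseen. The plan wants to estimate event rates and carry them into later trials. In a safety endpoint, under-counting is the unfavourable direction of error.

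**Working it through.** **1. The plan's own figures.** With 10 per arm, the Miettinen-Nurminen 95% interval for the difference has width 0.742 at equal rates of 0.2 and 0.820 at 0.5, matching the stated 0.74 to 0.82. The detection probability is 1 − 0.85^10 = 0.803, matching 80%. Drop-out is 4/24 = 16.7%, matching about 17%. None of these depends on the V5 window.

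**2. Assumptions.** The documents give no SAE rate for this population. I assume a 90-day risk P and constant hazard, so risk by day T is 1 − (1 − P)^(T/90).

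**3. Effect of the visit date on one patient's risk.**

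| Assumed P | Day 76 | Day 90 | Day 104 |
|---|---|---|---|
| 20% | 17.2% | 20.0% | 22.7% |
| 30% | 26.0% | 30.0% | 33.8% |
| 40% | 35.0% | 40.0% | 44.6% |
| 50% | 44.3% | 50.0% | 55.1% |

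**4. Does the window bias the comparison?** Take visit days uniform over the same window in both arms, 12 per arm. The expected arm difference is 0. The SD of the difference in mean visit day is (window length/√12) × √(2/12): 1.65 days for +14 and 3.30 days for ±14. At P = 30% the hazard is −ln(0.7)/90 = 0.00396 per day, so risk rises by about 0.0027 per day at day 97 and 0.0028 at day 90. The chance SD is then about 0.4 points (+14) or 0.9 points (±14). Simulation gives the same values, and 0.3 to 0.6 or 0.7 to 1.3 points over P = 20% to 50%. The half-width of the 95% CI is about 34 to 41 points (10 or 12 per arm, rates 0.2 to 0.5).

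**5. Effect of early loss on one arm's crude percentage.** If k of 12 leave at day L and the rest are followed to day 90, the expected percentage is ((12 − k)/12) × P + (k/12) × [1 − (1 − P)^(L/90)].

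- P = 30%, k = 2, L = 30: 0.2500 + (2/12) × 0.1121 = 26.9%.
- P = 20% and 50%, same k and L: 0.1667 + (2/12) × 0.0717 = 17.9%; 0.4167 + (2/12) × 0.2063 = 45.1%.
- P = 40%, k = 2, L = 7: 0.3333 + (2/12) × 0.0390 = 34.0%. With L = 45: 0.3333 + (2/12) × 0.2254 = 37.1%.
- P = 30%, k = 1, L = 30: 0.2750 + (1/12) × 0.1121 = 28.4%.

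**6. Both effects together.** If the ten remaining patients are seen mid-window at day 97, full follow-up would give 1 − 0.7^(97/90) = 31.9%. The crude figure is (10/12) × 0.319 + 0.0187 = 28.5%. Loss pulls the percentage down and a late V5 pushes it up, so the crude figure is not the risk at any stated day.

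**The case against.** **The ±14 belongs to exploratory sampling.** Where a window is given for V5 itself or for adverse event recording, it is +14. That stands, and it makes the discrepancy small. It still needs reconciling, because both windows describe the same visit.

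**A reader might infer that the arms are compared over different times at risk.** The documents do not support this. Both arms share one window under 1:1 randomisation and double blinding, so the expected arm difference from the window is zero and the chance imbalance is trivial against the CI. Follow-up could differ by arm only through differential withdrawal or loss, which nothing in the text suggests.

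**A reader might also build a large spurious advantage.** At P = 40%, losing all four expected drop-outs from one arm at day 7 gives (8/12) × 0.40 + (4/12) × 0.039 = 28.0%, 12 points below the true risk. That is a constructed extreme. If four drop-outs fall at random, all are in a given arm with probability 495/10,626, about 4.7%, even before requiring day 7.

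**The loss is smaller than 17%.** The 17% includes serious protocol violators, who need not be lost. Patients who only stop the product stay in follow-up, and death is itself an SAE. All of this stands. The bias comes only from consent withdrawal or loss before any SAE.

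**The rest is for the SAP, and a crude percentage is conventional.** Censoring rules may well be in an SAP that is not shown, and the analysis is declared descriptive. The crude percentage is not an error, and cutting it off at day 90 would drop SAEs from days 91 to 104. It should therefore stay. But the article does fix the measure and its end point, and that percentage alone does not estimate risk over a defined period.

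**Conclusion.** The point holds in limited form. The V5 window is contradictory and must be reconciled. The primary SAE percentage covers unequal times at risk and counts early leavers as event-free, so it understates each arm's risk over the intended follow-up. With 2 of 12 lost, the illustrations show shortfalls of about 2 to 6 percentage points (20.0% to 17.9%; 30.0% to 26.9%; 40.0% to 34.0%). With 1 of 12 lost at day 30 and a 30% risk, the shortfall is 1.6 points. These rest on assumed 90-day risks, constant hazard and assumed days of loss. They are upper-side illustrations, since part of the 17% will not be lost to follow-up. The arm comparison is biased only if withdrawal differs by arm. No sample-size figure is affected.

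**What to change.** 1. Reconcile the sections to a single V5 window. The visit schedule and the adverse event recording period both use +14; the exploratory objectives are the exception.
2. Keep the crude percentage of patients with any SAE up to EOS, as stated.
3. Beside it, report the day-90 cumulative incidence of first SAE per arm by Kaplan-Meier, censoring at consent withdrawal or loss to follow-up and counting death as an SAE, with the difference and its 95% CI.

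Under a +14 window everyone who attends V5 is observed to day 90. Under ±14, patients seen before day 90 would have to be censored at that visit.

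The cost is a wording change and a little extra analysis. Adverse events are recorded continuously, so no new data collection should be needed. The estimates will be imprecise with 12 per arm, and Kaplan-Meier assumes that those who leave have the same later risk as those who stay. Reasons for withdrawal should therefore be listed by arm. SAEs after day 90 remain in the crude percentage.
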